**Sample size considerations**

A priori calculation of the sample size of patient participants to compare the intervention group to the historical control group in the primary outcome was performed with the software ‘*Power and Precision*‘*.* Based on an assumed medium to large effect size of 0.40, a statistical power of 80% and a significance level of 5% (two-sided) the minimum required patient sample of *N* = 100 per group was calculated. Further sample size considerations take into account the actual number of splenectomized patients insured by the AOK. An explorative request showed that 360-400 patients undergo splenectomy a year, resulting in approximately 500 patients assumed to be available for recruitment in the planned inclusion period of 18 months. Based on studies with similar patients (13), we further estimated a proportion of 50% non-respondents for the intervention group and attrition rates of 40% of respondents, so we aim to recruit 500 potential intervention group patients for an expected analysis sample of *N* =178 participants. As this exceeds the statistically required number of cases despite conservative estimations, sufficient cases will be available even after considering potential deceases in the course of the study.

Given that the inclusion period (18 months) is the same for the control group (although retrospectively), sample size considerations for this group are largely the same, with the exception of an assumed proportion of 60% non-respondents and a dropout rate of 50%, resulting in expected *N* = 110 control group cases for analysis. Correspondingly, the number of physician participants included in analysis will be *N* = 178 intervention patients’ physicians and *N* = 110 control patients’ physicians maximum, considering that some patients may have the same physician.

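### The expected analysis samples of 178 and 110 do not follow from the stated pool and loss rates, which give 150 and 100; no single pool yields both figures.

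*Protocol*

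**What the plan says.** All the figures stand in the Protocol, Sample size considerations.

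- **Requirement.** From an "assumed medium to large effect size of 0.40", with "a statistical power of 80% and a significance level of 5% (two-sided"), "the minimum required patient sample of *N* = 100 per group was calculated".
- **Supply.** The insurer's data show that "360-400 patients undergo splenectomy a year". From this the protocol takes "approximately 500 patients assumed to be available for recruitment in the planned inclusion period of 18 months".
- **Intervention group.** "we further estimated a proportion of 50% non-respondents for the intervention group and attrition rates of 40% of respondents". Starting from 500 potential patients, the expected analysis sample is given as 178. The next sentence reads: "As this exceeds the statistically required number of cases despite conservative estimations, sufficient cases will be available even after considering potential deceases" during the study.
- **Control group.** The inclusion period is described as equally long, though retrospective, and the reasoning as mostly unchanged, "with the exception of an assumed proportion of 60% non-respondents and a dropout rate of 50" per cent. The expected analysis sample is given as 110. No pool is stated for this group.
- **Physicians.** The maximum numbers of physicians are set at the same 178 and 110.

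**The concern.** Every input for the intervention figure is printed in the same paragraph, and the 40% is tied explicitly to respondents, so the order of the losses is fixed. A reader who multiplies them through does not reach 178. The control figure has the same problem if it rests on the same pool.

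At stake is whether the expected numbers can be relied on. They show a surplus of 78 and 10 patients over the required 100 per group. The control number also steers recruitment: according to Participants and recruitment, a second control cohort was contacted in order to reach the planned sample size. The same figures then cap the physician samples.

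**Working it through.** **1. The requirement reproduces.** Inputs: 0.40, read as a standardised mean difference (the protocol does not name the scale), 80% power, two-sided 5%, equal groups.

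n per group = 2 x (1.960 + 0.842)² / 0.40² = 2 x 7.85 / 0.16 = 98.1, rounded up to 99. The t-test solution is 99.1, hence 100 when rounded up. This agrees with the protocol.

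**2. The expected samples do not reproduce.** Expected n = pool x (1 − non-response) x (1 − attrition).

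| Group | Calculation from 500 | Result | Stated | Difference |
|---|---|---|---|---|
| Intervention | 500 x 0.50 x 0.60 | 150 | 178 | 28 (28/150 = 19%) |
| Control (500 implied) | 500 x 0.40 x 0.50 | 100 | 110 | 10 (10/100 = 10%) |

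**3. Which inputs would give the stated figures?**

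- Pool at the stated rates: 178 / 0.30 = 593 for intervention; 110 / 0.20 = 550 for control.
- Attrition from a pool of 500: 1 − 178/250 = 28.8% instead of 40%; 1 − 110/200 = 45% instead of 50%.

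**4. Can one pool give both?** With a common pool the two samples must stand in the ratio 0.30/0.20 = 1.50. The stated ratio is 178/110 = 1.62. A pool of 593 gives 178 and 119; a pool of 550 gives 165 and 110. The yearly rate over 18 months is 360 x 1.5 = 540 to 400 x 1.5 = 600, giving 162 to 180 intervention and 108 to 120 control patients. Each stated figure lies in its range, but they do not come from the same pool.

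**5. Another arithmetic route.** Dividing by one plus the attrition rate gives 250 / 1.4 = 178.6, close to 178. The same step for controls gives 200 / 1.5 = 133, not 110. It is not a correct way to apply a loss rate, and it does not explain both numbers.

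**6. Effect on power.** Unadjusted two-sample t-test, standardised difference 0.40:

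| Intervention / control | Power |
|---|---|
| 178 / 110 (as stated) | 91% |
| 150 / 100 (recomputed) | 87% |
| 100 / 100 (stated minimum) | 80% |

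With 150 intervention patients, about 74 controls already give 80%. Check by normal approximation: 0.40 x √(150 x 74 / 224) = 2.82, and 2.82 − 1.96 = 0.86, which corresponds to about 80%.

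**The case against.** The strongest reply is that the control error is inferred. The protocol gives 500 only as the number of potential intervention patients and states no control pool. Controls were found by a retrospective database search and contacted in two rounds. A pool of 550 lies inside the 540 to 600 implied by the yearly rate and gives exactly 110. This stands in part: the control shortfall of 10 is conditional on 500, whereas the intervention shortfall of 28 is not. But 550 appears nowhere, and a separate control pool sits badly with equal inclusion periods and reasoning said to be mostly unchanged. Either the figure or the missing pool needs correcting.

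Three stronger readings are tempting, and the document does not support them.

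- **That the control group has no margin, so power is at risk.** It has no margin over the stated 100, but that minimum assumes equal groups. With 150 intervention patients the comparison tolerates about 26 fewer controls (100 − 74) before unadjusted power reaches 80%.
- **That the assurance about deaths is false.** That sentence follows the intervention figure and precedes the control paragraph. At 150 the group is still 50 above 100. Under Procedure, only intervention patients are measured after the telephone session, so deaths during follow-up do not reduce the control outcome data.
- **That propensity score adjustment takes power below 80%.** The protocol gives neither the imbalance in the score nor the outcome variance it explains. The first costs precision and the second can restore it, so no figure can be derived from the document.

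**Conclusion.** The expected samples are wrong as written. The intervention figure is overstated by 28 on inputs that are all stated. The control figure is overstated by 10 if the pool is 500, as implied; otherwise it rests on an undisclosed pool of about 550. The two figures cannot share a pool at the stated rates.

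The consequence is limited. The required 100 per group stands, both recomputed groups meet it (the control group exactly), and unadjusted power falls from about 91% to about 87%, still above the 80% target. These power figures assume that 0.40 is a standardised mean difference and that the comparison is an unadjusted two-sample t-test. This is a planning figure to correct, not evidence that the trial is too small.

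**What to change.** In Sample size considerations:

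- State the number of patients approached for each group, including the control group.
- Make pool, loss rates and expected samples agree. On the stated inputs the samples are 150 and 100. If another base was used, print it and recompute from it.
- Change the maximum physician numbers to match (150 and 100 on the stated inputs).
- Keep the sentence on sufficient numbers after deaths, but name the intervention group in it so that it is not read as covering controls.

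The cost is protocol wording only. Hypothesis, required sample size and analysis stay as they are; the printed surplus becomes smaller.

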**Outcome measures**

***Primary outcome***

*The primary outcome*, the adherence to preventative measures, is indicated by a study-specific ‘Preventing PSS-score (PrePSS-score), which includes the following parameters: (1) receipt of guideline-conform pneumococcal and (2) meningococcal vaccinations, (3) prescription and availability of stand-by antibiotics for emergency treatment and (4) handing out of and carrying a medical alert card for asplenic patients. The selection of the included parameters was made by infectious diseases specialists of the University Medical Centre Freiburg based on current prevention recommendations.

To weight these preselected parameters, an expert survey was conducted prior to the study asking a total of sixteen international experts in the care of asplenic patients to rate the items according to their importance in infection prevention, of which nine experts provided feedback. Based on the calculated median of the given expert-ratings the scoring system was defined (see Table 1 for an overview, for exact score formation and operationalization see supplement). The score for each patient is estimated by the study physicians according to both the patient’s and the practitioner’s information gathered through telephone-interviewing. To validate the self-report data on the primary outcome, health insurance patient routine data aggregated by groups (number of vaccinations relevant to asplenia and prescribed emergency antibiotics) will be included.

**Table 1**: Parameters and scoring system of the PrePSS-score

| **Parameter** | **Score range** |
| --- | --- |
| (1) Guideline-conform sequential pneumococcus vaccination | 0-3 |
| (2) Guideline-conform meningococcal vaccination | 0-3 |
| (3) Stand by-antibiotic prescribed and available (‘pill in the pocket‘) | 0-2 |
| (4) Handing-over and carrying a medical alert card | 0-2 |
| **Maximum total PrePSS-score** | **10** |

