**Intervention**

The intervention comprises a telephone-based individual intervention session for patients with asplenia and a separate intervention for their general practitioner, conducted by study physicians of the Medical Center - University of Freiburg with expertise in clinical infectious diseases. The content of the intervention was developed based on comprehensive literature review, existing guidelines for infection prevention and the study physicians’ expert knowledge. Both, the intervention sessions for patients and for their physicians are manual-guided to ensure a consistent practice across all study physicians; however, the interview protocol is semi-structured to allow an individualized proceeding. When developing the manual, particular attention was paid to its practical feasibility to enable a future implication beyond this study.

Prior to the implementation of the intervention, all participants are sent patient or physician tailored educational materials with brief information on the prophylaxis options along with a comprehensibly prepared vaccination plan and a medical alert card for asplenic patients (5^th^ Ed.), which was developed by the Medical Center – University of Freiburg, the German Society of Infectious Diseases and the German Sepsis Society.

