**Procedure**

The chosen outcomes for patients are measured prior to the intervention (baseline measurement, t0), directly after the intervention (t1) and after a 6-month follow-up period (t2).

At t0, patients in the intervention group are sent paper-pencil pseudonymized questionnaires on baseline proximal and distal secondary outcomes and socio-demographic information. Upon receipt of the filled questionnaires, telephone appointments are arranged with patients for a study physician interview by study nurses. During telephone calls, a vaccination history, use and availability of stand-by antibiotics and the medical alert card are taken to gather baseline data on the primary outcome, the PrePSS-score, along with some other medical information relating to the patients’ asplenia (e.g. indication for splenectomy, splenectomy date and previous episodes of infection or PSS requiring hospitalization)

After t0-data collection, the patient-directed telephone-intervention is implemented. The intervention of the corresponding physician is conducted at about the same time; however, the order is determined by the arrangement of the telephone appointments and not standardized. Secondary physician outcomes are gathered after the physician-directed intervention. Historical control group patients and their physicians go through the same procedure and patients receive t0-questionnaires identical to intervention group patients, but only intervention participants continue measurement after the telephone intervention.

Following each patient telephone call, intervention patients complete post-intervention questionnaires on the proximal secondary outcomes similar to baseline items and evaluate the telephone-intervention (t1).

To test for six-month sustainability of the effects of the intervention they receive follow-up questionnaires on distal secondary outcomes identical to baseline measurement (t2). After return of the follow-up questionnaires, intervention patients are contacted by study physicians via telephone again to inquire the same set of data on the primary outcome and (changes in) medical data, such as the incidence of infections and PSS, gathered at t0.

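### The team that coaches intervention patients also takes and scores their six-month primary outcome, while controls are scored before any session, so the parts resting on the patient's word are open to one-sided over-reporting

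*Protocol*

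**What the plan says.** Three sections of the protocol give the same group of staff three roles.

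- **Coaching.** Intervention: the patient and practitioner sessions are "conducted by study physicians of the Medical Center - University of Freiburg with expertise in clinical infectious diseases". In the patient session the participant chooses which recommendations to follow and makes action and coping plans with the physician, including for the risk of forgetting the card.
- **Interviewing.** Procedure: after the six-month questionnaires come back, "intervention patients are contacted by study physicians via telephone again to inquire the same set of data on the primary outcome".
- **Scoring.** Primary outcome: "The score for each patient is estimated by the study physicians". The same sentence adds that both the patient's and the practitioner's telephone information are used, and the section refers exact scoring rules to a supplement.

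Controls go through the t0 procedure only, and their data are complete before their shortened session (Procedure; Short version of the patient-directed intervention). The main analysis compares the intervention group's follow-up score with the control group (Data analysis).

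The protocol has two safeguards. Self-reported primary-outcome data are confirmed with the practitioner at t0 and, in the intervention group, at t2; where the practitioner was interviewed first, patients are told of discrepancies when required (Procedure). Insurer data on vaccinations and emergency antibiotics, aggregated by group, serve as validation (Primary outcome).

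**The concern.** At t2 an intervention patient is asked about the very behaviours that he or she planned with a member of the interviewing team. The patient may wish to give the agreed answer. The physician, who knows the group, may score leniently when the answer reflects on the team's own work. A control patient answers the same questions with no such history. Any resulting excess enters the main comparison mainly on one side. It is a measurement error that depends on group, so a propensity score built from covariates does not correct it. The limitations in the Discussion name self-selection, lack of randomisation and the weighting of the score, but not this.

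At stake is whether a modest difference in the PrePSS-score shows better prevention or more favourable reporting.

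**Working it through.** **1. Which components can be checked?** Table 1 gives 0-3 points each for pneumococcal and meningococcal vaccination, and 0-2 each for the stand-by antibiotic and the alert card.

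| Component | Practitioner | Insurer data (group level) |
| --- | --- | --- |
| Vaccinations | yes | yes |
| Antibiotic prescribed | yes | yes |
| Antibiotic at hand | not readily | no |
| Card handed over | partly (practitioners are asked to fill in fields on it) | no |
| Card carried | not readily | no |

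The two exposed components belong to items worth 2 + 2 = 4 of 10 points. The split within each item is in the supplement, which is not shown, so 4 is an upper bound. The confirming practitioners have also been coached by the same team (Physician-directed intervention), so at t2 their confirmation is not fully independent.

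**2. The plan's own figure.** Sample size considerations: "Based on an assumed medium to large effect size of 0.40", 80% power, two-sided 5%.

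n per group = 2(1.960 + 0.842)² / 0.40² = 2 × 7.85 / 0.16 = 98.1, so 99. The t-based solution is 99.08, so 100. The stated 100 per group is reproduced.

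**3. Illustration of the effect on the test.** The inputs are the plan's expected analysis samples, 178 and 110. The protocol gives neither the SD of the score nor an over-reporting rate. Assumptions: SD of 2 to 3 points, no true effect, a simple two-group comparison, and a mean excess b that exists only in the intervention group.

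- SE in SD units = √(1/110 + 1/178) = 0.1213.
- Rejection rate = P(|Z + (b/SD)/SE| > 1.96).
- b = 0.2, SD 3: 0.067/0.1213 = 0.55; P(Z > 1.41) + P(Z < -2.51) = 0.079 + 0.006 = 8.5%.
- b = 0.2, SD 2: 0.10/0.1213 = 0.82; P(Z > 1.14) + P(Z < -2.78) = 0.128 + 0.003 = 13.1%.

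| Mean excess (points) | SD 3 | SD 2.5 | SD 2 |
| --- | --- | --- | --- |
| 0.2 | 8.5% | 10.1% | 13.1% |
| 0.3 | 13.1% | 16.7% | 23.5% |
| 0.5 | 27.9% | 37.8% | 54.0% |

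With 100 per group, an excess of 0.2 points gives 7.6% to 10.9%.

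A mean of 0.2 points arises if 20% of patients over-report by 1 point (0.20 × 1) or 10% by 2 points (0.10 × 2). For scale, the planned 0.40 SD is 0.8 to 1.2 points. The smallest significant difference at 178 versus 110 is 1.96 × 0.1213 = 0.24 SD, or 0.48 to 0.71 points.

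**The case against.** The strongest reply is that the score is not bare self-report. The practitioner's information goes into it, confirmation takes place at both time points, and insurer data provide an outside check. This stands for vaccinations and prescriptions. It does not reach availability and carrying.

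A reader might go further than the protocol allows in four ways.

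- *That the same physician coaches and re-interviews each patient.* The protocol does not say so. It only sets no rule against it, and assignment may be governed by a manual that is not shown.
- *That all 4 points of the antibiotic and card items are unverified.* Prescription can be checked, and hand-over of the card partly.
- *That the error can only favour the intervention group.* Controls also speak to a university physician and may give desirable answers. All participants are sent materials and a card before the intervention, and the protocol does not fix whether this precedes the t0 interview. Only the difference between groups is bias.
- *That the bias is a known share of the planned effect.* The documents give no figure for it. The table covers any intervention-only excess, not just the part caused by meeting the coach again.

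It is also fair to say that a different study physician still belongs to the coaching team. The remedy is partial.

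**Conclusion.** The point holds in limited form. Coaching, t2 interviewing and scoring lie with one staff group, no rule separates coach from assessor, and controls are scored before any session. Over-reporting of the patient-only components, or lenient scoring, would mainly favour the intervention group and would survive propensity adjustment.

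The size cannot be derived from the documents. The figure of about 8.5-13% false positives instead of 5% shows only that a small mean excess matters at these sample sizes. It rests on an assumed SD of 2 to 3, an assumed excess of 0.2 points with no offsetting over-reporting in controls, and 178 versus 110 patients analysed. The required sample size is unaffected. This is a worthwhile low-cost improvement and does not show that the primary comparison is invalid.

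**What to change.** - **Procedure.** State that each t2 telephone interview is taken by a study physician who did not deliver that patient's session. The Intervention section speaks of study physicians in the plural, so existing staff should suffice, although their number is not given.
- **Primary outcome.** State that the interviewer records the component answers and that the score is derived from them by the supplement's fixed rules, with the group label removed where this is possible. Judging vaccinations probably needs dates, and these may reveal the group.
- **Reporting.** Present the components that rest on the patient alone (antibiotic at hand, card carried) separately from those confirmed by the practitioner, so that readers can see whether the difference depends on them.

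The cost is some scheduling and data-handling effort, and a t2 interviewer who is new to the patient. Sample size, visits and the intervention stay as they are. The bias is reduced but not removed: the interviewer still knows the group, and the patient has still been coached. The Discussion should list this as a limitation.

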***Secondary outcomes***

In this article secondary patient outcomes are classified on a proximal-distal continuum of outcome measures (25). HAPA-related variables (i.e. patient’s risk perception, self-efficacy and action-planning) are considered as *proximal secondary outcomes* which are assumed to be more likely and directly affected by the intervention than distal outcomes and observable shortly after the intervention. More global, *distal secondary outcomes,* are assumed to be also influenced by proximal outcomes as well as external, non-treatment factors. These include disease knowledge (disease knowledge is also expected to be a confounder), patient general and asplenia-specific self-management as well as asplenia-specific health literacy, self-reported patient involvement and health-related quality of life.

*Secondary outcomes for physician participants* are their subjective improvement in knowledge and their satisfaction with the intervention.

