**Participants and recruitment**

Participants are patients with anatomic asplenia and their physicians (general practitioner or specialists). Eligible are German-speaking patients aged 18 years or older, who are insured by the cooperating health insurance AOK Baden-Württemberg, which is Germany’s 5^th^ largest health insurance and insures more than four million people.

Patient participants are preselected to either the intervention or control group based on the time interval since they underwent splenectomy. Patients who are recently splenectomized (at most 4 months) are allocated to the intervention group. Potential intervention patients are recruited about 6-8 weeks after splenectomy successively by biweekly request from February 2019 for a maximum period of 18 months. The historical control group consists of patients who are splenectomized since more than six months (at most 18 months). Thus, pre-interventional baseline-data on primary and secondary outcomes in the historical control group account for routine care. Potential control group patients were recruited at the start date of study implementation (January 2019) and, to attain the planned sample size, another cohort of patients was contacted half a year later (June 2019).

Potential patient participants are identified via a database search for all splenectomized patients within the predefined group-specific time periods since splenectomy by assistants of the AOK-Baden-Württemberg. Patients who meet criteria receive recruitment letters from the health insurance. Those who are interested in study participation receive detailed information on the procedure, the aims and the legal conditions of the study from the University Medical Centre Freiburg. Participants are asked to provide written informed consent and contact information if they agree to take part. Participants who participate in another clinical intervention trial at the same time are excluded from data analysis.

To identify potential physician participants, participating patients are asked to provide contact information on their general practitioner or other physician who mainly cares for their asplenia and sign an agreement releasing the practitioner form medical confidentially obligation. Physicians whose patients consent to having their physicians included in the study are recruited by letters with information concerning the study. No exclusion criteria for physicians are applied.

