**Questionnaires**

Patient-related secondary outcome measures, potentially confounding variables and the patients’ evaluation of the telephone-intervention are assessed via self-administered paper-pencil questionnaires incorporating already validated instruments as well as asplenia-specific scales developed for the purpose of this study, which are described below.

1. ***HAPA-related outcomes*.** To gather key HAPA variables addressed in the intervention, perceived disease risk relevant to asplenia, patients’ behavioral intention to implementation, perceived self-efficacy for implementation, action and coping planning, positive and negative outcome expectations and received social support are assessed. Items were developed on the basis of the general assessment rules for HAPA constructs provided by Schwarzer et al. (20) and slightly adapted to infection prevention behavior in asplenia. Responses are rated on a six-point scale ranging from *fully correct* (1) to *not correct at all* (6) (except the scale *risk perception*)*.*

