**Data analysis**

Demographic characteristics of the study population and effect sizes in the intervention group will be reported descriptively. The main analysis tests the hypothesis that the PrePSS-score at follow-up is higher (better adherence to infection-risk reducing preventive measures) in the intervention group than in the control group. Due to the non-randomized design a propensity score adjustment is performed to reduce potential bias that may be caused by differences on covariates in the two groups (36). We will apply general linear models with propensity score as a covariate. The same method will be used for the analysis of secondary outcomes. Assuming missing data in the questionnaires, multiple imputation will be considered for corresponding analyses. Additional analyses will be conducted with structural equation modeling technique to test a priori specified mediation models of intervention effects.

A cost-effectiveness analysis of the intervention will be conducted by analyzing the change-from-baseline scores of the primary and the secondary outcomes in relation to the costs of the intervention. To reveal the economic efficiency of the intervention, routine data will be used to determine standard treatment and follow-up costs associated with infections requiring hospitalization and with PSS in asplenic patients to contrast them to the intervention costs.

In the qualitative analyses, the audio files of the interviews will be transcribed by an external service provider and the transcripts will be analyzed using a qualitative content analysis.

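### Disease knowledge is called a confounder as well as an outcome, but the controls' only knowledge value is taken together with their outcome; adjusting for it would bias the group effect if knowledge changes under usual care

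*Protocol*

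**What the plan says.** - **Two roles for one variable.** Protocol, Secondary outcomes, places disease knowledge among the distal secondary outcomes and states in the same sentence that "disease knowledge is also expected to be a confounder". Hypothesis (e) under Aims and hypotheses expects the intervention to raise it.
- **One instrument for both.** Protocol, Questionnaires, collects "Patient-related secondary outcome measures, potentially confounding variables" in the same paper forms.
- **Timing, intervention group.** Protocol, Participants and recruitment: "Patients who are recently splenectomized (at most 4 months) are allocated to the intervention group". They are approached about 6 to 8 weeks after surgery. Under Procedure, their distal outcomes and PrePSS-score are taken again at t2, after six months.
- **Timing, controls.** They are more than 6 and at most 18 months after splenectomy. Under Procedure they have t0 only. Participants and recruitment explains that "pre-interventional baseline-data on primary and secondary outcomes in the historical control group account for routine care", so their t0 data are their outcome data.
- **Adjustment.** Protocol, Data analysis, enters a propensity score as a covariate in general linear models and adds: "The same method will be used for the analysis of secondary outcomes". It does not list the covariates in the score.
- **Mediation.** The same section plans structural equation models to "test a priori specified mediation models of intervention effects".

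**The concern.** A confounder has to precede the exposure being compared. The intervention group's t0 knowledge meets that condition: it is taken before the telephone session. The controls' t0 knowledge does not. It is recorded after 6 to 18 months of usual care, in the same assessment as the outcome. The knowledge items ask about consequences of splenectomy and preventive measures, which is what post-splenectomy care teaches. Much of the PrePSS-score is history (vaccinations received, antibiotic prescribed, card handed over), so in controls adherence may also have produced the knowledge.

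Adjusting on this value compares early knowledge in one group with late knowledge in the other. A gap that only reflects the later measurement would be treated as confounding and moved into the effect estimate. When knowledge is itself the outcome, the control's outcome value could stand on both sides of the model. The mediation models share the timing problem: control mediators and control outcome come from one assessment and have no time order.

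**Working it through.** **1. The plan's reference effect.** Sample size considerations gives an effect size of 0.40, 80% power, two-sided 5% and 100 per group. Read as a standardised mean difference: n = 2(1.960 + 0.842)² / 0.40² = 98.1, so 99 per group; the t-based solution is 99.08, so 100. The figure reproduces, and 0.40 SD is a fair yardstick.

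**2. Inputs not in the documents (assumed).**
- g: change in knowledge under usual care between the early and the late assessment, in SD; 0.3 and 0.5 are shown.
- r: correlation of measured knowledge with the PrePSS-score; 0.2 to 0.4.
- ρ: correlation of early with late knowledge; 0.3 to 0.9.
- Group sizes 150 and 100, from the plan's own rates: 500 × 0.5 × 0.6 and 500 × 0.4 × 0.5. The protocol states 178 and 110; the size of the bias hardly depends on this.

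**3. Bias for adherence.** Suppose no true effect and no true difference between the groups. With knowledge as the only covariate, the propensity score is close to a linear function of it, so:

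adjusted effect = (outcome difference) − slope × (knowledge difference) = 0 − r × (0 − g) = r × g.

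The standard error is √(1/150 + 1/100) × √(1 − r²) / √(1 − R²). Here R² is the share of group membership explained by knowledge: 0.24g² / (1 + 0.24g²), which is 0.021 at g = 0.3 and 0.057 at g = 0.5.

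| g | r | Bias (SD) | Share of 0.40 | SE | Rejection at 5% |
|---|---|---|---|---|---|
| 0.3 | 0.2 | +0.06 | 15% | 0.128 | about 8% |
| 0.3 | 0.4 | +0.12 | 30% | 0.120 | about 17% |
| 0.5 | 0.2 | +0.10 | 25% | 0.130 | about 12% |
| 0.5 | 0.4 | +0.20 | 50% | 0.122 | about 37% |
| 0 | any | 0 | 0 | – | 5% |
| −0.3 | 0.4 | −0.12 | −30% | 0.120 | about 17% |

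A simulation with a logistic propensity score and 3,000 trials per setting agrees: +0.06, +0.12, +0.10 and +0.20 SD for the first four rows, with rejection rates of 7%, 16%, 11% and 36%.

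**4. Knowledge as the outcome and in the score.** In controls the covariate and the outcome are the same value, so the within-group slope is 1. In the intervention group it is ρ. The pooled slope is about 0.6ρ + 0.4, and the spurious effect is g(0.6ρ + 0.4). At g = 0.3:
- ρ = 0.3: 0.3 × 0.58 = +0.17 SD
- ρ = 0.5: 0.3 × 0.70 = +0.21 SD
- ρ = 0.7: 0.3 × 0.82 = +0.25 SD
- ρ = 0.9: 0.3 × 0.94 = +0.28 SD

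**5. Mediation.** No arithmetic applies. Intervention patients have t0, t1 and t2; controls have t0 only. Between-group paths therefore rest on control data in which mediator and outcome are simultaneous.

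**The case against.** **The adjustment is inferred.** Data analysis names no covariates, and such a list is commonly left to the statistical analysis plan. Other candidates are collected: socio-demographic data, indication for splenectomy, compliance items, PHQ-4. A reader might infer that the protocol puts knowledge in the score, or puts knowledge in the score for its own analysis. It says neither. This stands, and the point is therefore conditional. What remains is that the protocol itself gives knowledge the confounder label, and no analysis plan can supply an earlier control value.

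**The bias depends on drift.** The documents give no figure for drift and do not fix its direction. This stands too.

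**Leaving knowledge out has a price.** The groups are self-selected, with assumed non-response of 50% and 60%. If a 0.3 SD knowledge gap were a genuine pre-existing difference, omitting it would bias the effect by 0.3 × 0.4 = 0.12 SD, as much as the bias described here. The data cannot separate drift from confounding. This argues for showing both analyses, with the primary one free of a variable that may be a result of the care compared.

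**Mediation.** A reader might infer that the models should be fitted within the intervention group, where time order exists. That removes the group contrast, so it cannot test mediation of the between-group effect.

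**Conclusion.** The point holds in conditional form. Two facts stand in the protocol: disease knowledge has both roles, and the controls' only knowledge value is simultaneous with their outcome. If that value enters the propensity score and knowledge changes under usual care, the adherence effect shifts by about r × g. That is 15% to 50% of the planned 0.40 over the positive drifts shown, with the sign reversed if knowledge falls and no shift if it is stable. For knowledge as its own outcome, the shift at 0.3 SD drift is about +0.17 to +0.28 SD. All these sizes rest on assumed drift and correlations, and on a score built from knowledge alone.

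A reader might go further and infer that the trial's effect estimate is biased as planned, or that a false positive for knowledge is near certain. The documents support neither. A false-positive rate above 90% for knowledge appears only with an early-late correlation of about 0.7 or more; at 0.3 SD drift it is about 36% to 38% for a correlation of 0.3 and about 62% to 64% for 0.5.

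**What to change.** 1. Protocol, Secondary outcomes: remove the confounder label from disease knowledge for the group comparison.
2. Protocol, Data analysis: state that the primary propensity score uses only characteristics fixed at or before splenectomy and recorded alike in both groups (for example age, sex, education and indication for splenectomy), and never the outcome being analysed.
3. Present adjustment for t0 knowledge as a labelled sensitivity analysis, saying that the control value is simultaneous with the control outcome.
4. Label the between-group mediation models exploratory, because control mediators and outcome come from the same t0 assessment. Do not replace them with a within-group model.

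The cost is wording and one extra analysis; no new data are needed. The downside is that any genuine pre-existing difference in knowledge stays unadjusted in the primary analysis. The sensitivity analysis makes its possible size visible.
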